### Secondary outcomes

Clinical union will be measured during physical examination. Pain on axial compression force and pain on the fracture site during palpation will be monitored through a patient-based VAS score. When patients still report significant pain, measured as a VAS > 3 on a Visual Analogue Scale from 0 to 10 [31, 32], clinical union is not yet achieved. Return to sports is defined as the time (in weeks) to resumption of weight-bearing sports after surgery and the level should be maintained for at least 30 days [33]; return to work is defined in the same way. When returned to sport, but activity level decreases to below the start level within 30 days after resumption, then this will be deemed as a failed return to activity and the date will not be counted. From the 6^th^ till the 14^th^ week, most unions are expected to occur. On each of these biweekly time points a union rate will be counted; number of unions at t = XXX divided by total sample size (%).

The SF-36 is a patient-administered, generic health related quality of life instrument [34, 35]. The FAOS was developed to assess the patients’ opinion about a variety of foot and ankle-related problems [36]. The results can be presented as an outcome profile. The FAAM is a 29-item questionnaire. The FAAM consists of 2 subscales: Activities of Daily Living and Sports [37].

Cost-effectiveness is analyzed using the The EuroQol (EQ-5D) [38, 39] and the SF-36, FAOS, FAAM as measurement for effectiveness of treatment. Costs are calculated from the SF HLQ [40, 41] and the cost of the investigated intervention. The questionnaire consists of 11 questions and provides information about labor (missing) costs and additional paid working hours.

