### Data acquisition and follow-up

Participating patients will be assessed at the following time points (Table 1):

**Table 1 Tab1:** Schedule for screening and follow-up of included participants

Screening and Follow-Up Clinical and Radiographic Exams						
Action	Pre-operative	Intra-operative	Follow-Up Visit (biweekly 2-14 weeks)	Follow-Up Visit Until Union (biweekly) (>14 weeks, determined by physician)	6 month follow-up visit	1 year Follow-Up visit
Information letter	X					
Obtain written informed consent	X					
Complete eligibility checklist	X					
Complete medical history and baseline characteristics (form)	X					
Complete physical examination (form)	X		X	X	X	X
Surgery		X				
- Operative form (surgical information)		X				
- cB + cBMA preparation and administration		X				
- Bone biopsy fracture site		X				
Lab assessments	X					
Questionnaires	X		X		X	X
Radiographic assessment	X	X	X	X	X	X
Complication (form)	X	X	X	X	X	X
Adverse events, withdrawals & re-operation (form)	X	X	X	X	X	X

before inclusion: information letter, complete reliability checklistpreoperatively (after an enrollment period of two weeks): informed consent, complete reliability checklist, baseline characteristics (age, gender, weight, height, affected side, duration of symptoms, smoking status, AAS before symptoms and at preoperative assessment, past medical history, medication used), type of sport and profession, local physical examination with VAS, laboratory assessment (Hemoglobin levels, leucocytes, sodium, potassium, urea and creatinine), FAOS, FAAM, SF-36, EQ-5D, SF HLQ, X-ray (AP oblique and lateral);intraoperative: cB + cBMA preparation and administration, bone biopsy of the fracture site, right after internal fixation an X ray (AP, oblique and lateral) and an operative form (surgical information) with complications and (S)AEs if applicable;biweekly 2-14 weeks postoperatively: wound inspection, local physical examination with VAS, FAOS, FAAM, SF-36, EQ-5D, TiC, X-ray (best view for analyzing the fracture), resumption of sports and work, complications and (S)AEs;six months postoperatively: local physical examination with VAS, FAOS, FAAM, SF-36, EQ-5D, TiC, X-ray (best view for analyzing the fracture), resumption of sports and work, complications and (S)AEs;one year postoperatively: local physical examination with VAS, FAOS, FAAM, SF-36. EQ-5D, TiC, X-ray (best view for analyzing the fracture), resumption of sports and work, complications and (S)AEs

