## Statistical methods

An online, quality-assured, digital database will be created containing the data. The analyses will be performed with SPSS statistical package (version 17.0; SPSS, Chicago, Illinois). Patient’s demographics, gender, age, height, weight, affected side will be described for both treatment groups and safety will be assessed by identifying and summarizing complications and other clinically relevant adverse events collected throughout the study. Continuous data will be presented as the mean (and standard deviation) if normally distributed (according to Fischers exact or eyeball test); otherwise, the medians (with range) will be reported. Dichotomous data will be presented as frequencies (with accompanying percentages).

To check the distribution of the baseline characteristics, the treatment groups will be compared using Student’s t-tests or chi-square tests, depending of the type of outcome measure.

The primary endpoint – number of weeks until patients achieved radiological union postoperatively – will be analyzed using a student’s *t*-test or equivalent; this parameter will be used for clinical union as well. A chi-square test will be used to analyze union rate at each time point, and a student’s *t*-test will be used to determine statistical differences in time to return to work and/or sport. Patient-reported outcome measures will be analyzed using a student’s *t*-test or repeated measures ANOVA.

Risk factors for the development of healing problems (such as smoking behavior, BMI, and age) will first be identified using univariate analysis (t-tests, chi-squared tests). In case of significance (significance level will be set at 0.1), the risk factors will be entered in a multivariate logistic regression model. The cBMA analysis will be reported as absolute cell count and in % of cell types. Data on the bone biopsies of the stress fractures will be descriptive.

A comprehensive, updated sample size justification and statistical plan will be created together with an interim report after the interim analysis.

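### Return to sport names no level to be reached and turns on an undefined start level; on the stricter reading, no AAS is scheduled at follow-up to apply it

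*Protocol article*

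**What the plan says.** The definition is in the protocol article under Definitions, Secondary outcomes: "Return to sports is defined as the time (in weeks) to resumption of weight-bearing sports after surgery", with the condition that "the level should be maintained for at least 30 days". The failure rule covers this case: "When returned to sport, but activity level decreases to below the start level within 30 days after resumption". Such a return is classed as failed and its date is disregarded. For employment, "return to work is defined in the same way".

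Data acquisition and follow-up sets out what is measured and when. The preoperative list includes "AAS before symptoms and at preoperative assessment", together with the type of sport and the profession. The lists for the biweekly visits to week 14, for six months and for one year contain SF-36, EQ-5D, FAAM, FAOS and TiC, and end with "resumption of sports and work, complications and (S)AEs". None of them lists the AAS, and Table 1 shows only a general row for questionnaires.

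Statistical methods says that a Student's t-test "will be used to determine statistical differences in time to return to work and/or sport".

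**The concern.** The definition uses the word level twice and anchors it neither time. No level has to be reached for the event to occur, and the threshold for a failed return is not defined. Two readings are open: the level at which the patient resumed, or the level before symptoms. They can give different dates for the same patient.

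The two readings fail in different ways. The first can rank a modest but steady return ahead of a fuller one that was slightly eased. The second needs the activity level to be compared with its pre-symptom value during follow-up, and the AAS is not scheduled there.

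Time to return to work or sport is a named secondary endpoint, and Objectives and hypothesis expects an earlier return to sport or activity with the intervention. A result on this endpoint should mean one thing. If levels are not collected during follow-up, an analysis plan written later cannot recover them.

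**Working it through.** **The plan's own figures.** Inputs from Sample size: means of 12 and 10 weeks, SD 1.88, significance level 0.05 (taken as two-sided), power 90 %. The effect size is (12 − 10)/1.88 = 1.06. The two-sample t-test calculation gives 19.58, so 20 per arm, with power 0.906 at 20. Allowing for 20 % dropout, 20/(1 − 0.20) = 25. The figures reproduce. They concern radiographic union and do not involve this endpoint.

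**The rule applied to example paths.** The levels and weeks below are assumed for illustration; the article gives none. The pre-symptom level is set at 9 and first resumption at week 8. The 30-day window then closes at 8 + 30/7 = week 12.3. Easing on day 21 falls at 8 + 21/7 = week 11, inside the window. Easing on day 35 falls at 8 + 35/7 = week 13, outside it. Reading A takes the start level as the level at resumption. Reading B takes it as the pre-symptom level and treats any activity below that as not qualifying.

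| Assumed path | Reading A | Reading B |
|---|---|---|
| Level 3 from week 8, kept | week 8 | no date |
| Level 9 at week 8, eased to 8 at week 11, not regained | week 8 void; week 11 if the eased level counts as a new resumption, otherwise no date | no date |
| Level 9 at week 8, eased to 8 at week 13 | week 8 | week 8 |
| Level 9 at week 8, eased to 8 at week 11, level 9 again from week 16 and kept | week 11 if the eased level counts as a new resumption, otherwise week 16 | week 16 |

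**What follows.**

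1. Under A, the patient at level 3 is dated week 8. The patient who returned at 9 and eased to 8 is dated week 11 at the earliest, or not at all. The lower return gets the better time.
2. The third row bounds this: easing after the 30-day window does not void the date.
3. Under B the reversal is gone. The rule now requires knowing at follow-up whether the patient is at the pre-symptom level, and the AAS is itemised only for the two preoperative references.
4. The second and fourth rows show a further gap. The article does not say whether a later date replaces a voided one. A t-test needs one value per patient, so a patient without a replacement date has none to contribute.
5. Return to work takes over the same rule, so under A partial or light duties kept for 30 days would count as a return. The article does not say whether that is intended.

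**The case against.** The strongest reply is that reading B may be what was meant. The AAS before symptoms is collected, so a comparator exists, and on that reading the reversal does not occur. That stands: the perverse ordering depends on reading A and on easing within 30 days. Reading A is the more natural one, because the wording sits beside the level to be maintained and the time after resumption, but it is not the only one.

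Second, the article is a condensed account. The case report forms are not shown, and the item on resumption of sport and work may record a level. FAAM, with its Sports subscale, is collected at follow-up, so a merely light return need not go unseen. This also stands in part. It would be too strong to say that level cannot be known at follow-up. What can be said is that the AAS is not scheduled there and that the article ties neither the form item nor FAAM Sports to this endpoint. The ambiguity itself lies in a definition the article states, not in detail left out.

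Third, voiding a date does not drop the patient. Resumption is asked about up to one year, so a later date could be captured. That is right, but no rule says that it is used.

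Fourth, resumption at any level, held for 30 days, is a legitimate endpoint. It is, provided that it is labelled as such and the failure threshold is defined.

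A reader might go further and infer a bias of about 2 weeks, as large as the difference the trial calls clinically relevant. If six of 20 patients in an arm were dated at week 9 on one reading and week 16 on the other, that arm's mean would move by 6 × (16 − 9)/20 = 2.1 weeks. The documents do not support this as a treatment bias. Those inputs are assumed, the shift is between two readings within one arm, and the 2-week benchmark belongs to radiographic union. One definition applies to both randomised arms and patients are blinded, so the contrast would shift only if such patients were unevenly split.

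**Conclusion.** The definition needs repair on either reading. With the start level as the level at resumption, a sustained low-level return counts while a fuller return eased within 30 days loses its date. With the start level as the pre-symptom level, the AAS as scheduled does not allow the check at follow-up. The conclusion rests on the article's definition and itemised visit lists, and it would soften if the case report form for resumption records a level.

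The effect on a single patient can be several weeks, or a date against no date, in the assumed examples. No numerical bias between arms is shown. Nor does the article confine its return-to-sport hypothesis to athletes or soldiers; they appear in the Background, and the entry criteria do not restrict to them. This is a secondary endpoint, and the primary endpoint and sample size are unaffected. It is still worth correcting before data collection, because activity levels that were not recorded cannot be supplied at analysis.

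**What to change.** - Define the start level explicitly.
- Repeat the AAS at the visits that already record resumption of sport and work. Ask for the date on which the level was reached, since routine visits are sparse after week 14.
- Report two times: to the patient's own pre-symptom AAS held for 30 days, and to resumption at any level.
- State that after a failed return the next qualifying date is used.
- Treat patients with no qualifying date by one year as censored, and compare the arms with a time-to-event method, rather than omitting these patients from a t-test.
- For work, state whether partial hours or lighter duties count as a return.

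The cost is one short score per existing visit and a change of wording, with no added visits. Recorded times to the pre-symptom level will be longer than times to any resumption, and some patients will have no event by one year; the censored analysis is there to handle them.

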## Results

### Adverse events

Any (serious) adverse event during the trial period will be recorded. Adverse events are defined as any undesirable experience occurring to a patient receiving an investigational medical device that does not necessarily have to have a causal relationship with the device under investigation, e.g. infection, numbness, or paraesthesia. A serious adverse event (SAE) is any undesirable experience associated with the use of the investigational treatment that results in death, is life threatening (at the time of the event), requires hospitalization or prolongation of existing inpatients’ hospitalization, or results in persistent or clinically relevant disability or incapacity. All SAEs will be reported to the local Medical Ethics Committee within 15 days according to the regulations.

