**Methods/Design:**

A prospective, double-blind, randomized controlled trial (RCT) will be conducted in an academic medical center in the Netherlands. Ethics approval is received. 50 patients will be randomized to either operative treatment with cB + cBMA, harvested from the iliac crest, or operative treatment without cB + cBMA but with a sham-treatment of the iliac crest. The fracture fixation is the same in both groups, as is the post-operative care.. Follow up will be one year. The primary outcome measure is time to union in weeks on X-ray. Secondary outcome measures are time to resumption of work and sports, functional outcomes (SF-36, FAOS, FAAM), complication rate, composition of osteoprogenitors in cB + cBMA and cost-effectiveness. Furthermore, a bone biopsy is taken from every stress fracture and analysed histologically to determine the stage of the stress fracture. The difference in primary endpoint between the two groups is analysed using student’s *t*-test or equivalent.

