### Device description

The bone marrow required for the cB + cBMA treatment will be harvested from patient’s own iliac crest through needle aspiration. Two 30 cc syringes will be filled with bone marrow. Utilizing the MarrowStim Concentration System® (Biomet Biologics: Fig. 2) the bone marrow aspirate will be processed in a centrifuge (together with a counterbalance, 3200 rpm for 15 min); the poor cell plasma will be separated from the nucleated cell concentrate and the cBMA is realized (Fig. 3). No bone marrow will be collected from the patients within the control group; only a sham procedure will be performed by creating a similar skin incision on the same location on the iliac crest, to maintain patients’ blinding.

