### Standard treatment and investigational treatment

Experienced foot and/or ankle or trauma orthopaedic surgeons will perform the surgeries of both groups, within 2 weeks after inclusion. In brief, the proximal fifth metatarsal stress fracture will be approached and a decortication along the fracture lines will be performed. Part of this material will serve as a bone biopsy and is send for histological examination. The stress fracture will be internally fixated, with use of a cannulated intramedullary compression screw. The remaining material from the decortication will be used as an internal bone graft. The patients in the intervention group only will receive the cBMA mixed with 2 ml untreated autologous peripheral blood (cB + cBMA), together with the internal bone graft and serving as a natural scaffold; it will be put into and around the fracture. Of the 6 ml cB + cBMA obtained, 4 ml will be added to the fracture site the other 2 ml is used for analysis.

Both groups will receive a similar rehabilitation protocol for the first 8 weeks after operation; first two weeks in a non weight bearing-cast, then 2 weeks in a weight bearing cast or walker allowed to have partial weight bearing, thereafter 4 weeks in a weight bearing cast or walker without restrictions.

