### Outcome measures

The primary endpoint is the time to radiographic union in weeks.

The secondary endpoints are: time to clinical union, time to return to work and/or sport (in weeks), union rate at each time point (in %), patient function and satisfaction (SF-36, FAOS, FAAM), complication rate and cost-effectiveness (SF-HLQ), compared between intervention and control group.

During the operation a bone biopsy is taken. This will be histologically analyzed. From the obtained cBMA a 2 ml sample will be analyzed (flow cytometry and a multiplex assay for detecting CD 31, CD 34, CD 45, CD 90, CD 105, CD 166 amounts, CFU-F assay and mRNA analysis).

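### As worded, the adverse event definitions leave out the control arm, and the serious event definition adds an association test that the adverse event definition does not require

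*Protocol article*

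**What the plan says.** The definitions are in the protocol article, section Adverse events. For AEs: "Adverse events are defined as any undesirable experience occurring to a patient receiving an investigational medical device". The same sentence adds that the event "does not necessarily have to have a causal relationship with the device under investigation". For SAEs: "A serious adverse event (SAE) is any undesirable experience associated with the use of the investigational treatment", followed by a list of seriousness criteria (death, threat to life, hospitalisation or its prolongation, lasting disability). The section opens by saying that AEs, serious or not, are recorded throughout the trial. It closes by requiring SAEs to go to the ethics committee within 15 days.

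The control arm is described elsewhere. Device description: "No bone marrow will be collected from the patients within the control group; only a sham procedure will be performed". Standard treatment and investigational treatment: "The patients in the intervention group only will receive the cBMA". Abstract, Methods/Design: "The fracture fixation is the same in both groups, as is the post-operative care".

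On the use of harm data, Outcome measures lists complication rate among the secondary endpoints "compared between intervention and control group". Table 1 (Data acquisition and follow-up) has one form for complications and another for adverse events, withdrawals and re-operation. Both are ticked in all six columns, from pre-operative to one year, with no distinction by arm.

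**The concern.** In a sham-controlled trial the control arm shows how much harm comes from the operation itself. That requires the same definition of harm in both arms. Here the AE definition depends on receiving a device that controls do not receive, and the SAE definition depends on a treatment that they are not given.

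Two things are at stake. The first is participant protection. The sham incision is made only to keep patients blinded, and a serious event arising from it would fall outside the definition that triggers the expedited report. The second is comparability. Staff who follow the wording would label similar events differently by arm. Randomization states that patients and X-ray assessors are blinded, and it forbids study personnel from discussing allocation with the patient. Some personnel may therefore know the allocation when they judge whether an event is associated with the treatment.

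**Working it through.** The plan gives no figure on this point, so the check sets the passages side by side.

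**Step 1: what is the investigational device?** Device description names only the marrow concentration system. The screw cannot be what makes a patient a device recipient, because fixation is the same in both arms.

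**Step 2: who receives it?** Only the intervention arm does. Controls have no marrow collected and no concentrate placed.

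**Step 3: apply the wording to hypothetical events.** For the last two columns, assume that the event meets one of the seriousness criteria.

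| Event | AE? | SAE? | 15-day report? |
|---|---|---|---|
| Intervention arm, at the marrow aspiration site | Yes | Yes | Yes |
| Intervention arm, attributed to the screw fixation | Yes (no causal link needed) | Depends on how associated is read | Depends |
| Control arm, at the sham incision | No | No | No |
| Control arm, attributed to the screw fixation | No | No | No |
| Either arm, after randomisation but before surgery | No, on a strict reading: nobody has yet received the device | No | No |

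**Step 4: how many patients are affected?** Sample size plans 25 patients per arm. The share outside both definitions is 25 / (25 + 25) = 50%, which is the whole control arm.

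**Step 5: compare the two definitions.** The AE definition says that causality is not needed, while the SAE definition requires association with the treatment. SAEs are therefore not simply the serious subset of AEs. The second row of the table shows this within the intervention arm alone.

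**Step 6: compare the definitions with Table 1.** Table 1 schedules the AE form for participants at every visit, including the pre-operative one. Under the definition as worded, that form could hold no AE for a control patient at any visit, and none for anyone before surgery.

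**The case against.** The strongest reply is that the trial's procedures do not follow the literal definition. The Adverse events section opens with a general commitment to record events. Table 1 covers participating patients without regard to arm and starts before any device has been used. Quality assurance has the registration of adverse events monitored with no limit by arm. The probable intent is to collect from everyone. This stands, and it rules out any claim that control harms will go uncollected. It does not repair the definitions. The general commitment uses a term that the next sentence restricts, and a form does not say which events qualify for it. Nor can Table 1's silence on arm settle the matter: it also lists preparation and administration of the concentrate with no arm restriction, although only one arm receives it.

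A reader might go further and infer that control complications would be counted as zero and that the planned comparison of complication rates is invalid. The documents do not support that. Complications have their own form, and no passage says that a complication must first qualify as an AE. Statistical methods mentions complications together with other relevant adverse events, which suggests overlap but does not make the endpoint depend on the AE definition.

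It can also be said that associated need not mean judged causal, since the concentrate is placed during the same operation as the screw. That is fair for the intervention arm, and the table leaves that row open. It does not help controls, who have no use of the investigational treatment with which an event could be associated.

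Finally, the article condenses a full protocol that may hold better definitions, and it ties SAE reporting to the regulations. That is possible. The point here is not an omission, however: the article states both definitions, and they conflict with each other and with its own schedule.

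**Conclusion.** The definitions are wrong as written. On their wording, no event in any of the 25 control patients is an AE or an SAE, and a serious control event would not trigger the 15-day report. The SAE definition also imposes an association test that the AE definition does not require, and both conflict with Table 1.

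The consequence is a risk of asymmetric AE and SAE classification and reporting between arms. If the wording were followed, the asymmetry would make the intervention look worse. How much misclassification would occur cannot be estimated from the documents, because it depends on whether staff follow the definition or the forms. The complication-rate endpoint is not shown to be invalid. The primary endpoint, sample size and interim analysis are unaffected.

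The conclusion assumes that the investigational device is the concentration system and that the investigational treatment is the concentrate mixture, as the article's own sections describe them. It is a modest correction, worth making for participant protection and for like-for-like counting of harms.

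**What to change.** Reword the two definitions in the Adverse events section and add one data field:

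- **AE:** any undesirable experience in any randomised patient of either arm, over the period in which Table 1 schedules the AE form, regardless of relation to the device, the sham procedure or the operation. The period should include the pre-operative interval after randomisation and run to the one-year visit. Starting the clock at surgery would conflict with Table 1's pre-operative form, since randomisation takes place one day before the operation.
- **SAE:** any AE that meets the seriousness criteria already listed. The present opening, "any undesirable experience associated with the use of the investigational treatment", should lose its association condition.
- **Relatedness:** recorded as a separate field, so that it describes an event and does not decide whether the event counts.

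The cost is two sentences, one field and a few more reports to the ethics committee. The forms and visits already exist. The article describes the trial as about to begin inclusion, so on its own account the change could have been made before data collection.
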